## Abstract

**Background:**

Asthma is a common problem in children and, if inadequately controlled, may seriously diminish their quality of life. Inhaled short-acting beta2 agonists such as salbutamol are usually prescribed as ‘reliever’ medication to help control day-to-day symptoms such as wheeze. As with many medications currently prescribed for younger children (defined as those aged 2 years 6 months to 6 years 11 months), there has been no pre-licensing age-specific pharmacological testing; consequently, the doses currently prescribed (200–1000 μg) may be ineffective or likely to induce unnecessary side effects. We plan to use the interrupter technique to measure airway resistance in this age group, allowing us for the first time to correlate inhaled salbutamol dose with changes in clinical response. We will measure urinary salbutamol levels 30 min after dosing as an estimate of salbutamol doses in the lungs, and also look for genetic polymorphisms linked to poor responses to inhaled salbutamol.

**Methods:**

This is a phase IV, randomised, controlled, observer-blinded, single-centre trial with four parallel groups (based on a sparse sampling approach) and a primary endpoint of the immediate bronchodilator response to salbutamol so that we can determine the most appropriate dose for an individual younger child. Simple randomisation will be used with a 1:1:1:1 allocation.

**Discussion:**

The proposed research will exploit simple, non-invasive and inexpensive tests that can mostly be performed in an outpatient setting in order to help develop the evidence for the correct dose of salbutamol in younger children with recurrent wheeze who have been prescribed salbutamol by their doctor.

**Trial registration:**

EudraCT2014-001978-33, ISRCTN15513131. Registered on 8 April 2015.

## Background

Asthma is a common problem in childhood that, if inadequately controlled, seriously diminishes quality of life [1]. Approximately one million UK children have been diagnosed with asthma, and almost all of them will have been prescribed a short-acting inhaled beta2 agonist (usually salbutamol) as a ‘reliever’ medication to help control their day-to-day symptoms. Inhaled salbutamol is thus one of the most commonly prescribed medicines for children in the UK and many other countries around the world.

The dose-response relationship of any medicine must be determined prior to regulatory approval. Such research is relatively straightforward to perform in adults, but more difficult for children. As a consequence, many medicines currently prescribed for children have not undergone age-appropriate testing and so may not be effective or may even induce unnecessary side effects. EU lawmakers have voted for this to change through an emphasis on such evaluation in children [2]. The bronchodilator efficacy of inhaled salbutamol in asthma has now been established in both older children and adults [3], as has the minimum effective dose in these two groups [4]. However, neither efficacy nor minimum effective dose has been established in younger children (defined as aged between 2 years 6 months and 6 years 11 months), despite inhaled salbutamol frequently being prescribed within this age group.

There are a number of consequences of our lack of knowledge in this area:There is much uncertainty about the optimal dose of a beta agonist to use for symptom relief (for example, a variation between individual doses of 2–10 puffs is common practice).There is uncertainty about the optimal dose of a beta agonist for measuring bronchodilator response in the diagnosis of asthma.There is uncertainty about whether to use a beta agonist or alternatives such as ipratropium bromide or montelukast for symptom relief.

A dose of 2–10 puffs of inhaled salbutamol (approximately 100 μg per puff) is currently prescribed in both primary and secondary care as ‘reliever’ medicine for young children suffering from recurrent wheeze, a common feature of asthma in this younger age range. This dose is almost always administered via a spacer device, as younger children are unable to coordinate their breathing in order to inhale the medication directly from a metered dose inhaler. Following inhalation, the dose of salbutamol biologically available in the airways depends on many factors, such as breathing technique and airway calibre.

The urinary salbutamol level 30 min after the administration of an inhaled dose is a reasonable surrogate measure of the biologically available dose [5]. However, there are no studies where a specific effort has been made to collect a urine sample from a young child in the same manner.

The biologically available dose of salbutamol in the airway elicits the airway bronchodilator response. It is difficult to monitor side effects in young children, who are often unable to report discomfort such as palpitations or irritability. ‘Hyper-activity’ is a poorly studied problem that is commonly reported by parents of young children prescribed relatively large doses of salbutamol. In adults and older children, the response of the airway to a inhaled bronchodilator can be measured as changes in airway resistance or expiratory airflow before and after the administration of the bronchodilator. Most measures of airway resistance or airflow require the active co-operation of the patient, but such co-operation is difficult to achieve in young children. Conventional pulmonary function measurements, such as forced expiratory volume in 1 second or peak expiratory flow rate, either are impractical or are relatively unreliable in younger children. However, a technique relying on the transient interruption of breathing (known as the interrupter technique) has been recently developed as a reliable test of airway resistance (Rint) in this age group. Recent consensus guidelines [6] support the use of Rint in this age group for the measurement of airway resistance and for determining response to bronchodilator medication.

Thus there is now the possibility of correlating inhaled salbutamol dose with clinical response (measured as change in Rint) in younger children in the age range 2 years 6 months to 6 years 11 months. It is therefore of importance to document the airway response to increasing doses of inhaled salbutamol in this age group. To do this we need to document airway response against 30-min urinary salbutamol, the best available estimate for the bioavailability of salbutamol in the lungs. With expert children’s nurse support, we believe that most young children can be persuaded to pass a sample of urine at about 30 min following inhalation. However, we cannot assume that this will happen in all children and have made this a secondary outcome of the trial.

The proposed work is likely to identify a population of children who do not show a satisfactory response to salbutamol. There is evidence from studies in older children and young adults that one reason for this poor response may be a genetic change in their beta2 receptor (Arg/Gly16) [7, 8]. The presence of this polymorphism can be identified by DNA analysis on a simple saliva sample, without the need for specialist pulmonary function equipment. As these samples can easily be obtained in primary care, we propose to investigate whether this polymorphism is an effective marker for poor salbutamol efficacy in these younger children.

Overall, the proposed research will exploit simple, non-invasive and inexpensive tests that can mostly be performed in an outpatient setting in order to help develop the evidence for the correct dose of salbutamol in younger children with recurrent wheeze who have been prescribed salbutamol by their doctor. It is possible that a small dose of salbutamol, such as 2 puffs (200 μg) is adequate for most of these children. If this is the case, larger doses, such as 1000 μg, should not be prescribed (as is current practice) as they may induce side effects in these children. Secondly, some younger children who are currently prescribed larger doses of salbutamol may in fact be ‘poor responders’ or ‘non-responders’ to salbutamol due to their genetic constitution. Such children may benefit from alternative ‘reliever’ medicines, such as ipratropium or montelukast.

## Trial design

This is a phase IV, randomised, controlled, observer-blinded, single-centre trial with four parallel groups and a primary endpoint of the immediate bronchodilator response to salbutamol so that we can determine the most appropriate dose for an individual younger child. Simple randomisation will be used, with a 1:1:1:1 allocation (see the CONSORT flowchart of Fig. 1).

**Fig. 1 Fig1:**
[figure not shown]
CONSORT flowchart for the OpSal trial

## Methods

### Participants, interventions and outcomes

Potential participants will be identified by members of the direct care team at the Royal Alexandra Children’s Hospital, Brighton in outpatient or inpatient wards or the children’s emergency department. The direct clinical care (doctor or nurse) team will then refer the patient and carer to the research nurse for further discussion regarding the study. If they are interested and are happy to meet the research nurse, this will be arranged. Where appropriate, the patient and carer are provided with a Patient Information Sheet (PIS). In some cases this material will be sent by post. An appointment is arranged at the hospital, where any further queries are addressed. Eligibility criteria are established by the doctor and consent obtained at this visit. Informed consent, where offered, will be received by the research nurse on the day the child attends the study. The research nurse will have already provided written information on the study to both carers and children so they will have had time to consider the information prior to attending their appointment with the research nurse. The nurse will also show pictures of the Rint and saliva collection equipment and demonstrate the equipment. We will ensure that the child and the carer fully understand the implications of the consent and that they understand that the consent is voluntary and will not affect their treatment rights.

#### Eligibility criteria

Inclusion criteria

The inclusion criteria are as follows:Children between the ages of 2 years 6 months and 6 years 11 monthsHistory of recurrent wheeze, defined as at least three episodes of wheeze over the previous 12 months

Exclusion criteria

The exclusion criteria are as follows:Other major airway or lung disease, e.g. physician-diagnosed chronic lung disease of prematurity, cystic fibrosis or abnormal airway anatomyUse of long acting beta2 agonists within 1 week of the study visitTreatment with systemic corticosteroids or leukotriene inhibitors within 2 weeks prior to the study visit.Involvement in a drug study within the last 30 days

### Measuring dose response to inhaled salbutamol using Rint

To span the entire plausible dose-response range in each individual child would be unethical, requiring an impractical long protocol and multiple Rint measurements, at an age when cooperation is notoriously difficult to achieve and maintain. We therefore plan to map out the dose-response curve using a sparse-sampling dosage schedule in which each individual child will receive just two successive doses, with Rint measurements at baseline and after the first and second dose. For the dose-response assessment using Rint, we used the same design as the one created by two of the investigators for a recent study (DORESI study NCT 01470755). There is an assumption that the measurements made after administration of the second dose reflect the sum of the first and second doses, i.e. that the two doses are additive, with no loss of potency for the first dose during the interval between the first and second measurements. The two doses to be administered in each individual child will be randomly determined from the options below and will be concealed from the researchers measuring the response using Rint. Children will be randomised to the four dosage schedules in the ratio 1:1:1:1.

### Dosage schedules

The dosage schedules are as follows:100 μg salbutamol → +300 μg = 400 μg salbutamol100 μg salbutamol → +500 μg = 600 μg salbutamol200 μg salbutamol → +600 μg = 800 μg salbutamol200 μg salbutamol → +200 μg = 400 μg salbutamol

Thus these four dosage schedules will contribute the following data points to the dose-response curve covering the range 100–800 μg (Table 1).

**Table 1 Tab1:** Schedule of dose pairs to be tested

Dose studied	100 μg	200 μg	400 μg	600 μg	800 μg
1	√		√		
2	√			√	
3		√			√
4		√	√		

A schedule of assessments is given in Table 2.

**Table 2 Tab2:** Schedule of assessments

Schedule items	Enrolment	Randomisation	Baseline	Testing: Dose 1	Testing: Dose 2
Time point				T_0_	T_45 min_
Enrolment					
Eligibility screening	X				
Informed consent/assent	X				
Allocation		X			
Interventions					
Dose 1				X	
Dose 2					X
Assessments					
Clinical history	X				
Recent relevant medications	X				
Adverse events				X	X
Saliva sample (for DNA work)			X		
Rint assessment			X	X	X
Urine sampling				X	X

Rint measurement will be performed at baseline and 15 min after each of the two doses of salbutamol. The second dose of salbutamol will be given 30 min after the first dose. If the participant needs to take a bronchodilator within 12 h of the study visit, then the research appointment should be rescheduled. Rint measurements will be made as specified in the consensus guidelines [6]. Briefly, the child will be seated and breathing quietly through the apparatus, via a mouthpiece, with nose occluded by noseclip or fingers and with cheeks supported. If the child is unable to tolerate or use a mouthpiece, a facemask will be used for all three measurements. At each Rint measurement, a minimum of 10 flow interruptions will be carried out, with inspection of mouth pressure transients in real time, in order to achieve a minimum of five technically acceptable interruptions. The Rint measurement will be calculated as the median value of all acceptable interruptions.

All participants will be prescribed a salbutamol inhaler from ring-fenced hospital stock, stored within the research office and dispensed by the research nurse. The inhaler will be labelled according to EU requirements. The salbutamol inhalers will not be temperature-monitored. An accountability log of the doses given, when and to whom will be kept by the research team. After administration of the protocol-defined dose, the inhaler will be returned to the research nurse, the accountability log updated and the inhaler transferred back to the clinical trial pharmacy for destruction. Salbutamol inhalers are licensed products, and for this trial they are being used in line with established practice, supported by guidelines, and the dosage schedule does not exceed what would be stated in the participant’s GP prescription.

### Collection of saliva for DNA analysis

Saliva samples will be collected in accordance with the instructions provided by the manufacturers of the sampling kits. Trial participants will be asked to spit directly into a container; for children unable or unwilling to spit we will collect saliva samples using swabs.

We will use the non-invasive Oragene® DNA collection kits (http://www.dnagenotek.com) for the collection of saliva for DNA extraction. The kit provides a median DNA yield of about 110 μg. The DNA from saliva is stable in this kit for up to five years at room temperature due to proprietary reagents that inactivate bacteria and nucleases in saliva and minimize chemical hydrolysis of DNA. The DNA will be stored in the Clinical Investigation and Research Unit, Brighton and Sussex University Hospitals Trust (BSUHT). It will be shipped as a single batch to the Medical Research Institute, University of Dundee at the end of the study for storage in their DNA bank prior to DNA extraction and Arg/Gly analysis at codon 16 of the beta2 adrenoreceptor gene.

### Collection of urine 30 min after each dose of inhaled salbutamol

We will endeavour to collect a urine sample from each trial participant 30 min after each dose of inhaled salbutamol, as an additional check on the exact dose delivered to the lungs and therefore absorbed into the circulation. Given the age of these children, it may be necessary to accept some variation in the timing of the sample. The research team includes an experienced paediatric nurse with expertise in gaining cooperation from very young children. The urine samples will be stored frozen at −80 °C in the Clinical Investigation and Research Unit (BSUHT) and at the end of the study shipped as a single batch to the School of Pharmacy and Biomedical Sciences (University of Brighton) for salbutamol analysis using liquid chromatography and mass spectrometry (LC/MS).

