### Study of the relationship between urinary salbutamol levels and Rint measurements

The concentration of salbutamol in the urine at 30 min following a dose of salbutamol represents the gold standard of lung bioavailability. This has been established in adults. We will try to collect as many urine samples as possible, and we will aim to study the dose that is available to the lungs, measured as the 30 min urine salbutamol, against bronchodilator response. Data analysis will be performed as discussed above for inhaled lung dose versus bronchodilator response. As the production of urine on request is rather uncertain in children of this age, this is intended as a distinct secondary analysis. The main project, including the principal outcomes, will not be affected in any manner if the collection of these samples is incomplete.

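### On the text timing, the first urine sample falls due as dose 2 is given (Table 2 conflicts), so a late first void mixes both doses while the first Rint reading reflects dose 1 only

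*Protocol article*

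**What the plan says.** All references are to the protocol article.

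- **Dose 2 time.** The text under Dosage schedules says: "The second dose of salbutamol will be given 30 min after the first dose". Table 2 in the same section heads the dose 1 column T0 and the dose 2 column T45 min.
- **Rint times.** Same section: "Rint measurement will be performed at baseline and 15 min after each of the two doses of salbutamol".
- **Urine times.** The urine collection section says: "We will endeavour to collect a urine sample from each trial participant 30 min after each dose of inhaled salbutamol". It then adds: "Given the age of these children, it may be necessary to accept some variation in the timing of the sample".
- **Meaning of the second Rint reading.** The section on measuring dose response says: "There is an assumption that the measurements made after administration of the second dose reflect the sum of the first and second doses".
- **Use of the urine value.** In the section on urinary salbutamol and Rint, "we will aim to study the dose that is available to the lungs, measured as the 30 min urine salbutamol, against bronchodilator response". On method: "Data analysis will be performed as discussed above for inhaled lung dose versus bronchodilator response". On status: "this is intended as a distinct secondary analysis".

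**The concern.** The urine level is meant to stand for the dose that reached the lungs, so that airway response can be set against it. That requires each urine value to belong to the same dose as the Rint reading it is paired with.

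On the text timing nothing separates the first sample from dose 2. The article itself expects some samples to be mistimed, and calls urine production on request uncertain at this age. A child who first voids a few minutes late gives a sample containing part of dose 2. If it is analysed as the dose 1 sample, it is paired with a Rint reading taken before dose 2 existed.

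The error is not plain noise. Dose 2 is 1 to 5 times dose 1, depending on the randomised schedule, so the same delay distorts exposure by different amounts in different arms. The shape of the exposure-response relation is at stake, not only its precision.

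**Working it through.** **Timeline from the text.** Dose 1 at T0; Rint at 0 + 15 = T15; urine 1 at 0 + 30 = T30; dose 2 at T30; Rint at 30 + 15 = T45; urine 2 at 30 + 30 = T60. The gap between urine 1 and dose 2 is 30 − 30 = 0 min.

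**Timeline from Table 2.** If T45 is the time of dose 2, it contradicts the text, and the gap after urine 1 is 45 − 30 = 15 min. If T45 is instead the second Rint time, it fits the text (30 + 15), but the dose 1 column should then read T15 and it reads T0. Neither reading makes text and table agree.

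**Assumption for sizing.** The article gives no excretion rate and no distribution of void times. I assume the amount excreted is proportional to dose, at a constant rate, with no lag. The void at 40 min is an example. Write d1 and d2 for the two doses in μg.

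**Late first void, at 40 min.** With dose 2 at T30, dose 1 contributes 40·d1 and dose 2 contributes 10·d2. Overstatement of dose 1 exposure = 10·d2 / (40·d1).

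**Second sample, at T60.** If the child voided at T30, it holds 30·d1 + 30·d2, exactly proportional to the cumulative dose. If not, it holds 60·d1 + 30·d2. Excess = 30·d1 / (30·d1 + 30·d2) = d1 / (d1 + d2).

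| Schedule (μg) | d2/d1 | Overstatement, first void at 40 min | Excess in second sample, no earlier void |
|---|---|---|---|
| 100 + 300 | 3 | 3000/4000 = 75% | 100/400 = 25% |
| 100 + 500 | 5 | 5000/4000 = 125% | 100/600 = 17% |
| 200 + 600 | 3 | 6000/8000 = 75% | 200/800 = 25% |
| 200 + 200 | 1 | 2000/8000 = 25% | 200/400 = 50% |

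**Same dose point, different urine.** Two schedules reach 400 μg. In arbitrary units, a child who voided at T30 gives 30 × 400 = 12,000 on either schedule. A child who did not gives 60 × 100 + 30 × 300 = 15,000 on 100 + 300, and 60 × 200 + 30 × 200 = 18,000 on 200 + 200.

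**If dose 2 is at T45.** A first void at 40 min contains no dose 2, so the overstatement is 0%. The second sample, at T75, holds 45·d1 + 30·d2 after a void at T30 and 75·d1 + 30·d2 without one. The excess is 30·d1 / (45·d1 + 30·d2): 3000/13,500 = 22%, 3000/19,500 = 15%, 6000/27,000 = 22% and 6000/15,000 = 40%. Dependence on earlier voiding therefore remains on either reading.

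**Sensitivity to the excretion profile (dose 2 at T30, first void at 40 min).** Across constant-rate excretion and first-order excretion with half-times of 30 and 240 min, the dose 2 share of the sample is 43–51% for 100 + 300 and 200 + 600, 56–63% for 100 + 500, and 20–26% for 200 + 200. A lag before salbutamol appears in urine would lower these shares, and a lag of 10 min or more would remove them for a void at 40 min.

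**The case against.** **Dose 1 belongs in the second sample.** A reader might infer that every second sample is contaminated and that the urine analysis as a whole pairs response with the wrong dose. The article does not support that. It treats the second Rint reading as the response to both doses together, so cumulative exposure is the right partner for it. Under constant-rate excretion with a void at T30, the dose 1 share of the second sample (25%, 17%, 25%, 50%) equals dose 1's share of the cumulative dose and shows no error. This objection stands. What survives it is the narrower point that the value shifts with earlier voiding. Exact proportionality is itself a feature of the constant-rate assumption: with a 30-min half-time the share on 100 + 300 is 14%, not 25%.

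**Simultaneity is not settled.** Table 2 can be read as giving a 15-min margin. This stands, so the first-sample point is conditional on the text timing.

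**The detail may lie elsewhere.** Sampling windows, the order of void and dose, and handling of late samples may sit in the full protocol or SAP. Nor does the article say outright that a late first void would be labelled a dose 1 sample. The absence of such rules is not the point made here. The point is that two stated times coincide and a tolerance is stated on top. An unseen window could discard late samples, but it could not put time between two events set for the same minute.

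**It is secondary.** The article says its principal outcomes do not depend on urine, and the planned Rint models do not use it. This stands and limits the weight of the point.

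**Conclusion.** The point holds in a limited form. On the text timing, a first void after T30 can mix both doses while its natural partner, the Rint reading at T15, reflects dose 1 only. First samples taken before dose 2 are correctly paired.

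For a first void at 40 min, the overstatement of dose 1 exposure is 25% to 125% across schedules if dose 2 is at 30 min, and 0% if it is at 45 min. The second sample is 17% to 50% higher without an earlier void if dose 2 is at 30 min, and 15% to 40% higher if it is at 45 min. All these figures rest on assumed constant-rate excretion without lag and refer to amounts excreted. They show direction and dependence on schedule, and do not estimate the bias in this trial.

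The primary Rint comparison and the genotype question are not affected.

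**What to change.** 1. Reconcile the dose 2 time in the Dosage schedules text with the Table 2 heading.
2. Record the actual time of each dose and each void in the case report form.
3. Treat only samples voided before dose 2 as dose 1 samples, and set them against the first Rint reading.
4. Set any sample voided after dose 2 against the second Rint reading and the cumulative dose, with an indicator for whether the child voided between the doses.
5. Use total salbutamol recovered over all voids only if urine volumes are already recorded. The article describes a concentration and mentions no volumes, so this step is not free.

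**Cost.** Steps 1 to 4 need a timing entry and revised analysis wording, with no extra samples. The downside is that fewer children contribute to the dose 1 urine analysis. The change was still practical when the article was written: 37 of the planned 156 children had been recruited, leaving 156 − 37 = 119, and the urine is stored frozen for one analysis batch at the end of the study. For children already seen, the classification depends on whether void times were noted.
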